## Introduction

### A global mental health emergency

A recent epidemiological study from 204 countries and territories highlighted approximately 53 million cases of major depressive disorder and 76 million cases of anxiety disorders directly linked to the pandemic. Notably, the younger population experienced the most significant increase, with women being twice as affected as men by these disorders [1].

In Italy, the Mental Health 2021 report published by the Italian Ministry of Health in 2022 stated that 778,737 individuals sought assistance from public specialist mental health services during 2021. Furthermore, nationwide data showed that 3.3% of emergency room admissions (n = 479,276) were related to psychiatric issues. Among individuals seeking assistance for mental health-related problems, 14.6% resulted in hospitalization, while 72.1% were managed at home. Thus, 7 out of 10 individuals seeking mental health services do not present with severe enough conditions to require hospitalization but require some form of psychological support, nonetheless. Moreover, 39.6% of all admissions are diagnosed with neurotic and somatoform syndromes [2]. Available data supports the evidence that the current public mental health system does not adequately address chronic cases, sub-clinical severity, or those that do not involve emergency management.

According to the 2022 Organisation for Economic Co-operation and Development (OECD) report titled “Health at a Glance: Europe,“ there was an increase in unmet needs for mental health care during and after the pandemic, with 23% of adults reporting such conditions in spring 2022, compared to 20% in spring 2021. While comprehensive data remains limited, national estimates indicate that the prevalence of depressive symptoms during the pandemic was approximately twice as high as pre-pandemic levels in numerous European countries [3]. Also, when looking at children and adolescents, recent estimates from the World Health Organization indicate that one in six individuals aged 10–19 have a mental disorder, with depression, anxiety, and behavioral disorders being the primary causes of distress [4]. Similar figures have been confirmed in Italian adolescents by a recent literature review by Deolmi & Pisani (2020) that emphasized the high prevalence of anxiety and depressive symptoms among young Italians attributed to the pandemic, social isolation, and parental stress [5].

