## Methods

### Study design

The PsyCARE study includes observational studies that are both cross-sectional and longitudinal. The University of Milan-Bicocca coordinates the study in collaboration with the University of Bergamo, the University of Catania, the University of Palermo, the University “La Sapienza” of Rome, and the National Board of Italian Psychologists.

The research study strictly adheres to the ethical guidelines outlined by the American Psychological Association (APA) and the principles outlined in the Declaration of Helsinki (seventh revision, 2013). The Ethical Committee of the University of Milan-Bicocca approved all materials and procedures.

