### Sampling plan

Data collection will include two samples. The first sample will consist of therapists registered with the National Board of Italian Psychologists, adhering to the Italian Psychologist Bonus initiative. The second sample will consist of participating therapists’ patients encompassing adults over 18 years old and adolescents aged between 14 and 18 using the Psychologist Bonus.

Therapists are recruited via online newsletters and web news promoted by the National Board of Italian Psychologists. Patients are recruited via their therapists’ participating in the study.

Before participating in the study, all participants will provide informed consent. For under-age participants, informed consent will be obtained from adolescents and their parents/legal guardians. Participation is entirely voluntary. As an incentive for enrollment, therapists can participate in a training course on psychological assessment for free and obtain forty out of the fifty yearly professional mandatory training credits [31].

Each therapist is assigned a unique six-letter reference code (i.e., ABCDEF). To ensure patients’ matching, the therapist will assign their unique code and a number for every patient enrolled (i.e., ABCDEF-1 for patient number 1, ABCDEF-2 for patient number 2, etc.). All self-report questionnaires are completed via a secure web link to ensure anonymity on the Qualtrics platform.

Our target sample size, is a minimum of 450 therapists and 450 patients (adults and adolescents) to achieve sufficient power for the study.

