To assess the economic impact of the PB (Objective 3), we will conduct a cost-effectiveness analysis (CEA) [64]. The calculation will include both direct and indirect costs between the baseline (T0) and post-intervention (T1) assessments. Direct healthcare costs will encompass the costs of the psychological intervention and any related healthcare costs. These costs will be compared to data on standard care from the Italian Ministry of Health to calculate the incremental costs of the intervention. Indirect costs, or productivity losses, will be estimated by multiplying the number of days of work/university/school lost due to psychological problems (as reported by participants) by an average daily wage (for work) or an estimated cost of a lost day of education (for university/school). The effectiveness of the intervention will be measured using the EQ-5D, which will be used to estimate Quality Adjusted Life Years (QALYs). The incremental cost-effectiveness ratio (ICER) will be calculated as the cost difference between the PB intervention and standard care from T0 to T1, divided by the difference in QALYs over the same period. The resulting ICER will represent the additional cost per QALY gained by the PB intervention compared to standard care. A sensitivity analysis will be conducted to test the robustness of our findings to changes in key assumptions or parameters, including the unit costs used to calculate direct costs and the valuation of lost productivity. This analysis will be conducted in accordance with standard guidelines for conducting and reporting CEAs, such as the Consolidated Health Economic Evaluation Reporting Standards (CHEERS) statement [65]. The power analysis from the *pwr* package in R [66] indicated that for a paired t-test with a small effect size (Cohen’s d = 0.20), a power of 0.80, and a significance level α = 0.05, you would need a sample size of approximately n = 199 pairs of observations.

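### The ICER is claimed against standard care, but only its cost side has a standard-care source; no standard-care QALYs are collected, sourced or assumed.

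*Protocol article*

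**What the plan says.** The Data analyses section of the protocol article sets out the cost-effectiveness analysis in four parts.

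- Numerator: "The incremental cost-effectiveness ratio (ICER) will be calculated as the cost difference between the PB intervention and standard care from T0 to T1".
- Denominator: "divided by the difference in QALYs over the same period".
- Interpretation: "The resulting ICER will represent the additional cost per QALY gained by the PB intervention compared to standard care".
- Source of standard-care data, given directly after direct healthcare costs are defined: "These costs will be compared to data on standard care from the Italian Ministry of Health to calculate the incremental costs of the intervention".

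QALYs are to be estimated from the EQ-5D. The patients who complete it are the therapists' patients, described under Sampling plan as "encompassing adults over 18 years old and adolescents aged between 14 and 18 using the Psychologist Bonus". Under Study design, "The PsyCARE study includes observational studies that are both cross-sectional and longitudinal"; no comparison group is described. Productivity losses are to be valued from the days that participants report losing.

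Aims and hypotheses defines the benefit for Objective 3 as the change in users between T0 and T1. The sample-size statement for this objective is a paired t-test with d = 0.20, power 0.80 and α = 0.05, giving about 199 pairs.

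**The concern.** An ICER is a ratio of two differences taken against the same comparator. Here the cost difference is taken against standard care, but nothing in the article supplies what standard care would have done to quality of life. The only QALY difference that the described data can yield is a before-after change in PB users. Dividing an incremental cost by a before-after change does not give the quantity that the article says the ratio will represent.

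The cost side has a smaller gap of the same kind. The Ministry data are linked to direct costs, and no comparator is described for participants' productivity losses.

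Hypothesis 3, that the PB is cost-effective, rests on this ratio. The Discussion says that the study's data may help to justify future funding. The comparative claim is therefore the one most likely to be used outside the study, and it is the one that the described data cannot support.

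**Working it through.** **1. The plan's own figure.** For a two-sided paired t-test with d = 0.20, α = 0.05 and power 0.80, the normal approximation is ((1.960 + 0.842)/0.20)² ≈ 196.2, so 197. The noncentral t solution is 198.15, rounded up to 199. The stated 199 pairs reproduce. A paired test is a within-person contrast, which agrees with Objective 3's definition of benefit as users' T0 to T1 change.

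**2. Which terms of the ICER have a source.** The claimed quantity is

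ICER = (C_PB − C_SC) / (ΔQ_PB − ΔQ_SC),

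where C is cost from T0 to T1, ΔQ is QALY change relative to baseline, and SC is standard care.

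| Term | Source in the article |
|---|---|
| C_PB, direct | Cost of the intervention and related healthcare |
| C_SC, direct | Ministry of Health data |
| C_PB, productivity | Days lost, reported by participants |
| C_SC, productivity | None described |
| ΔQ_PB | EQ-5D in PB users |
| ΔQ_SC | None described |

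Without ΔQ_SC, the ratio that can be computed is (C_PB − C_SC)/ΔQ_PB. The two ratios agree only if ΔQ_SC = 0.

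**3. Size of the discrepancy.** Write ΔQ_SC = f × ΔQ_PB, with ΔQ_PB and the incremental cost both positive and f < 1. Then

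true ICER / computed ratio = 1/(1 − f).

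The documents give no value for f, so these values are assumptions:

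| f | Meaning | 1/(1 − f) |
|---|---|---|
| −0.50 | Standard-care patients worsen | 0.67 |
| 0 | No change | 1.00 |
| 0.25 | A quarter of the gain occurs anyway | 1.33 |
| 0.50 | Half | 2.00 |
| 0.75 | Three quarters | 4.00 |

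**4. Illustration in euros.** The documents give no utilities or incremental costs, so everything here is assumed except the 180 days within which the benefit must be used. Assume a PB utility gain of 0.10, linear over 180 days, and an incremental cost of EUR 600. The QALY gain is 0.5 × 0.10 × 180/365 = 0.0247, and the before-after ratio is EUR 24,333 per QALY. If standard-care utility rises by 0.02, 0.05 or 0.08, the true ICER is EUR 30,417, 48,667 or 121,667. If it rises by 0.10, the ICER is undefined. If it falls by 0.05, the ICER is 24,333/1.5 = EUR 16,222.

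**The case against.** The strongest reply is that the denominator does not name its comparator. Placed right after a cost difference against standard care, it can be read as PB minus standard care as well. This is also a condensed article: a pre-registration exists that is not at hand, the analysis is to follow CHEERS-type guidance, and the sensitivity analysis covers key assumptions through an open list. The source of comparator QALYs might be stated elsewhere.

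The grammatical point stands, but it does not repair the plan. On that reading the article claims a difference whose second term has no data, model or assumption behind it, while Objective 3 and its sample-size statement are both before-after. The sensitivity parameters that are named concern costs. The article itself fixes the formula and its interpretation, so the mismatch is more than omitted detail.

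A reader might infer three stronger points, which the documents do not support.

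- **That the ratio necessarily favours the PB.** Natural improvement would have that effect. However, the Discussion warns that inadequate public provision risks conditions becoming chronic or worsening, and in that case the computed ratio would count against the PB.
- **That the Ministry costs describe a sicker group, so the PB would come out as dominant.** The Introduction does say that "the current public mental health system does not adequately address chronic cases, sub-clinical severity, or those that do not involve emergency management". But the article does not say which Ministry data will be used, and the Ministry report it cites covers a mix: 14.6% of those seeking help were hospitalised and 72.1% were managed at home. If this group gets little public care, standard care could equally be cheap, which would raise the incremental cost.
- **That n = 199 is wrong.** It is correct for a pre-post change, and Hypothesis 3 does predict that participants' quality of life will improve. It simply says nothing about the precision of an ICER.

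**Conclusion.** The concern holds as a mismatch between the ratio that the described data can produce and the interpretation given to it. The computed ratio equals the claimed ICER only under an unstated assumption of zero QALY change under standard care. With a positive incremental cost, the true ICER would be 1.33 to 4 times the computed one for f from 0.25 to 0.75, and lower than the computed one if standard-care patients would decline. These values of f are assumptions, and neither the size nor the direction of the bias can be settled from the article. The missing standard-care QALYs are missing from this document; whether another document supplies them cannot be judged here. The arithmetic of the 199 pairs is sound.

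**What to change.** Choose one of two routes before the analysis.

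1. Remove the comparison with standard care from the interpretation. Report Objective 3 as costs alongside the within-cohort QALY change, and state that reading the ratio of the two as incremental assumes no change without the PB.
2. Keep the ICER and give its comparator content. Specify standard-care QALY scenarios that include worsening, no change and partial improvement, together with costs for a comparable non-urgent population. State how productivity losses under standard care are handled. Report the ICER across these scenarios.

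Under either route, add a sentence saying that n = 199 pairs applies to the pre-post EQ-5D change and not to the ICER.

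The cost is a change of wording and, for the second route, a small scenario table. No new data collection from patients is needed. The price is a less definite statement about cost-effectiveness.

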## Discussion

The PsyCARE study’s primary goal is to provide systematic data on the Italian Government’s “Psychological Bonus” effectiveness in promoting access to psychological treatments. The study breaks ground in several ways.

First, the PB represents a first-time national initiative due to its promotion by the Ministry of Health outside the public healthcare system. However, funding is limited as only 10.52% of applicants will be allowed to benefit from professional interventions for psychological problems. The situation of public services in Italy has shown their struggle in responding to the great demand for intervention for psychological problems that do not require urgent treatment. This insufficient response risks contributing to the chronicization or worsening over time of situations that, if intercepted earlier, might instead have a different prognosis. Thus, the PsyCARE study will help provide more information on the effectiveness of the psychological interventions funded by the PB, both in lowering patients’ psychological distress and providing a cost-effective measure. Thus, the study’s data may help justify future financial allocations and influence policymakers to strengthen public and private services.

Secondly, PsyCARE will gather real-world data on the effectiveness of psychological interventions in reducing symptoms, with a particular focus on anxiety and depression. Indeed, the study seeks to integrate cross-sectional perspectives and evaluate the effects of short-term psychological interventions. The study’s results will potentially significantly contribute to the ongoing debate in psychotherapy regarding the role and impact of specific versus nonspecific therapeutic factors.

Third, in line with recent advancements in psychotherapy research, we aim to adopt a patient-specific, or “tailored,“ approach, exploring “what works for whom,“ as described by Peter Fonagy: indeed, the PsyCARE will provide findings to identify the therapeutic elements associated with patients’ improvement and determine which patients may benefit the most from the bonus sessions and specific psychotherapeutic techniques adopted [67, 68]. For example, we will consider between-subjects variability on the longitudinal trajectories of psychological symptoms accounting for different diagnostic presentations and controlling for the therapists’ different theoretical frameworks. Moreover, the study will allow the evaluation of the effectiveness of a psychological intervention through the observation of transdiagnostic factors (i.e., emotion regulation, epistemic trust) to open a window of understanding of the mechanisms of change that can be influenced by psychological interventions and can, in turn, contribute to the reduction of symptomatic manifestations.

Fourth, the PsyCARE study aligns with the need to make scientific results replicable. Indeed, one of the major limitations of research in psychology is the inability to replicate the results of studies on different samples. Although the study guarantees a sufficient number for the reliability of its results, it will be necessary to replicate its findings in other contexts and populations. Thus, all data and materials will be available on the Open Science Framework [69].

Finally, the limitations of the study will be acknowledged in the study implementation and in interpreting its results. For example, the evaluation of patients may be time-consuming. However, collaboration and engagement of therapists in the study may decrease the rejection rate from patients. In addition, the evaluation will be done by administering self-report instruments, which could lead to bias in interpreting the results. However, collecting the therapist’s perspective might also help account for possible bias. Moreover, as PsyCARE includes longitudinal data collection, we might expect participants to withdraw or drop out of the study. Thus, statistical analysis will have to account for attrition to assess the robustness of the findings (i.e., sensitivity analyses). Finally, as both new patients and patients already in treatment could benefit from the PB, the number of sessions might represent a confounding variable in evaluating the psychological interventions’ efficacy. Thus, data analyses will account for these differences and explore any variability in longitudinal trajectories of relevant variables between patients already in treatment and new ones.

## Data Availability

Datasets generated and analyzed during the current study and statistical materials will be available on the Open Science Framework (OSF) project page (https://osf.io/u3apv/). The study’s pre-registration is available on the OSF [70].

## List of abbreviations

ISEE: Equivalent Economic Situation Indicator
RCT: Randomized Controlled Trial
IAPT: Improving Access to Psychological Therapy
CBT: Cognitive Behavioral Therapy
NICE: National Institute for Health and Care Excellence
GAF: Global Assessment of Functioning
CORE-10: Clinical Outcomes in Routine Evaluation-10
ERQ: Emotion Regulation Questionnaire
GAD-7: General Anxiety Disorder-7
PHQ-9: Patient Health Questionnaire
ETMCQ: Epistemic Trust, Mistrust, and Credulity Questionnaire
EQ-5D: Euro Quality of Life-5D
YP-CORE: Young Persons’ Clinical Outcomes in Routine Evaluation
YSR: Youth Self Report
EQ-5D-Y: Euro Quality of Life-5D-Youth
CPPS: Comparative Psychotherapy Process Scale
CEA: Cost-Effectiveness Analysis
QALYs: Quality Adjusted Life Years
CHEERS: Consolidated Health Economic Evaluation Reporting Standards
